##### Demographic measures

Date of birth, sex, home living situation (i.e. living alone, with a partner or with friends), number of children aged <18 years living in the household, highest education level and ethnic origin were assessed by questionnaire.

##### Psychological measures

These include:A TPB questionnaire, based on recommendations by Ajzen [33], to assess the theory’s major constructs as related to becoming more physically active: attitude, subjective norm, perceived behavioural control and intention. Each construct was assessed with five questions, measured on a 5-point Likert-type scale. Examples are: “Increasing how much physical activity I do over the next 12 weeks will be: harmful through to beneficial” (attitude); “The people whose opinions I value would approve of me increasing how much physical activity I do over the next 12 weeks”: strongly disagree through to strongly agree (subjective norm); “It is up to me whether or not I increase how much physical activity I do over the next 12 weeks”: strongly disagree through to strongly agree (perceived behavioural control); “I intend to increase how much physical activity I do over the next 12 weeks”: strongly disagree through to strongly agree (intention);A similar TPB questionnaire designed to assess constructs related to physical activity self-monitoring. Each of the constructs (attitude, subjective norm, perceived behavioural control and intention) was assessed with questions measured on a 5-point Likert-type scale. Examples are: “Paying regular attention to how much physical activity I do over the next 12 weeks will be: harmful through to beneficial” (attitude); “The people whose opinions I value would approve of me paying regular attention to how much physical activity I do over the next 12 weeks”: strongly disagree through to strongly agree (subjective norm); “It is up to me whether or not I pay regular attention to how much physical activity I do over the next 12 weeks”: strongly disagree through to strongly agree (perceived behavioural control); “I intend to pay regular attention to how much physical activity I do over the next 12 weeks”: strongly disagree through to strongly agree (intention);A conscientiousness questionnaire consisting of two questions measured on a 7 point Likert-type scale ranging from 1 (disagree strongly) to 7 (agree strongly). Questions were “I see myself as dependable, self-disciplined” and “I see myself as disorganised, careless”.

##### Self-reported health behaviours

Self-reported physical activity was assessed using the validated Recent Physical Activity Questionnaire (RPAQ) [34]. Functional status was assessed using the validated SF-8 health survey questionnaire [35] which includes items on general health, physical functioning, limitations due to physical health, bodily pain, vitality, social functioning, mental health and emotional stress. Perceived stress was assessed using the validated 4-item Perceived Stress Scale (PSS-4) [36]. The PSS-4 consists of four questions aimed at assessing feelings and thoughts during the past month, measured on a 5-point scale ranging from 0 (never) to 4 (very often). We used the Self-Report Habit Index (SRHI) [37] to assess habit strength for physical activity. The SRHI is a 12-item instrument that assesses prior behaviour, automaticity and identity expression using a 5-point scale ranging from 1 (strongly disagree) to 5 (strongly agree). Gym membership, smoking status, vitamin supplement use, frequency of self-weighing and current medication use were each assessed by questionnaire.

##### Degree of intervention use

Participants’ degree of intervention use will be assessed by: 1) degree of completion of the paper-based physical activity diary (for the Diary group); 2) total number of days in which physical activity was recorded on the accelerometer band from Imperative Health (Activity Band and Activity Band Plus groups), and 3) total number of times the Imperative Health website was visited (Activity Band and Activity Band Plus groups).

##### Other measures

Usual weekly leisure-time physical activity was assessed using the GLTEQ [24]. Presence of angina was assessed using the Rose Angina Questionnaire [38]. Participation in other research, GP advice not to exercise, beta-blocker use, pregnancy status, ability to walk briskly for ≥15 minutes, access to and ability to use a home PC and the internet, ability to use English language websites, likelihood of leaving job in next 4 months, self-report of doctor diagnosed diabetes, main study goal, job satisfaction, contact with other study participants, self-monitoring behaviour and use of physical activity advice websites were assessed by phone call/questionnaire.

##### Intervention evaluation

Following attendance at the follow-up visit, all participants were sent an evaluation questionnaire by email. Participants were asked four questions to determine satisfaction with participation in the study: ‘How much did you enjoy taking part in the study”, “How satisfied were you with the study”, “Would you like to continue with the study”, “Did taking part in the study raise your awareness of the amount of physical activity that you do?”. Participants in the three intervention groups completed additional randomised-group specific questions related to satisfaction and acceptability of the intervention.

#### Participant safety

The primary safety concerns for participants are cardiovascular and musculoskeletal events associated with the laboratory procedures of treadmill exercise testing and injuries sustained as a consequence of increasing physical activity during free-living (everyday life). The cardiorespiratory fitness test used was submaximal, and only undertaken following extensive screening procedures. If a participant had a positive Rose angina questionnaire [38] or an abnormal ECG then they were referred to a clinical member of the measurement team for a more detailed medical review. If there were clinical concerns then the treadmill test was terminated early and/or the participant referred to their GP. Supervising staff are trained and hold current cardio-pulmonary resuscitation certificates.

Given the nature of the interventions, the risk of excess injury is deemed to be minimal. Standard safety criteria set by Imperative Health (i.e., BMI ≤18 kg/m^2^ and high BP >160/100 mmHg) for use of their system were used as exclusion criteria at screening, thereby minimising any risk of harm to participants using these systems. Participants and their GPs were asked to inform the study team about any significant changes in health status over the 12 week course of the trial. Ranges for acceptable results were set for all clinical measures. If these ranges were exceeded the information was sent to the GP and the participant was informed and advised to consult their GP. The participant’s GP was informed of their patient’s involvement in the trial following the baseline visit if the participant had given written consent. The baseline and 12-week anthropometric and clinical measures were sent to the GP after the 12-week visit, unless the participant’s HbA_1c_ value was significantly raised at baseline (≥48 mmol/mol), in which case all available clinical and anthropometric values were sent to the GP after the baseline visit and the participant informed.

#### Sample size

Estimates used to calculate the total number of participants required for the *Get Moving* trial were taken from the ProActive trial [39], which had a similar study population to *Get Moving*. Participants’ mean (SD) PAEE at baseline in the ProActive trial was 0.116 (0.076) kJ/kg/min. 100 participants per group completing follow-up would allow detection of a difference of 0.03 kJ/kg/min in PAEE (which is equivalent to approximately 225–300 Kcals or 20 minutes of brisk walking per day) with 80% power at a 5% significance level. Since the analysis will adjust for baseline values in an ANCOVA model, and assuming a correlation between baseline and follow-up PAEE of 0.58 (as estimated in ProActive), 100 participants per group at follow-up would enable detection of a difference between groups in mean PAEE of 0.025 kJ/kg/min.

Participants’ mean (SD) for cardiovascular fitness at baseline in the ProActive trial was 3.2 (1.0) L/min with a correlation between baseline and follow-up of 0.88. After adjusting for baseline values, 100 participants per group enables detection of a difference between groups in mean cardiorespiratory fitness of 0.19 L/min with 80% power at a 5% significance level. Thus, we aimed to recruit 480 participants into the *Get Moving* trial with 120 in each of the four groups at baseline. This number will allow for an attrition rate of 17% (or 20 individuals) in each group, which we would expect given attrition rates in previous studies [27,39].

#### Statistical analysis

Baseline characteristics of the study population will be summarised separately within each randomised group. The co-primary outcomes, PAEE and cardiorespiratory fitness, will each be analysed using an ANCOVA that includes all participants in the group to which they were randomised, regardless of the intervention actually received (Intention-to-Treat analysis). The outcome in the ANCOVA model will be change (follow-up minus baseline) in PAEE (cardiorespiratory fitness), with the baseline value included as a covariate in the model. For each outcome a 3 degrees of freedom test will be performed of the null hypothesis that there is no difference between the 4 randomised groups. The ANCOVA model will also be used to derive estimates of the differences in mean change and 95% confidence intervals for each of the 6 pairwise comparisons: ‘*Diary*’ vs. ‘*Control*’, ‘*Activity Band*’ vs. ‘*Control*’, ‘*Activity Band Plus*’ vs. ‘*Control*’, ‘*Activity Band*’ vs. ‘*Diary*’, ‘*Activity Band Plus*’ vs. ‘*Diary*’ and ‘*Activity Band Plus*’ vs. ‘*Activity Band*’. Where baseline values of the outcome are missing, the missing indicator method will be used to enable these participants to be included in the analysis [40]. An analysis will be performed to check whether adjusting for age, sex and BMI (the randomisation stratifiers) in the ANCOVA model has any impact on the conclusions; if it has no impact, then they will not be included in the model.

For each continuous secondary outcome, the 6 pairwise differences between randomised groups will be estimated, together with 95% confidence intervals, using ANCOVA as described previously. Any continuous endpoints whose distribution is skewed will be log transformed prior to analysis, in which case a ratio of geometric means (and confidence interval) will be reported.

Subgroup analyses by sex and BMI (below/above median value) will be investigated for the 2 co-primary outcomes only.

Degree of use of the intervention will be summarised separately within each intervention group (i.e., the Diary, Activity Band and Activity Band Plus groups). The numbers and types of adverse events within each randomised group will be reported.

The primary analysis of outcomes will use an Intention-To-Treat population, which includes all participants in the group to which they were randomised, regardless of the intervention actually received. A secondary analysis of outcomes will use a Per-Protocol (PP) population. Inclusion in the PP population will be based on 1) degree of completion of the paper-based physical activity diary (for the Diary group); 2) total number of days in which physical activity was recorded on the accelerometer band from Imperative Health (Activity Band and Activity Band Plus groups), and 3) the total number of times the Imperative Health website was visited (Activity Band and Activity Band Plus groups). Degree of usage/completion will be defined once clean data are available (but before the start of any trial analyses), when the distributions can be inspected.

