#### Baseline assessment

On arriving at the measurement centre, having fasted for the preceding one hour (including abstaining from nicotine, caffeine and vigorous exercise), individuals provided fully informed written consent following a discussion about the study with the measurement team. Height, weight and blood pressure were measured first to check the third stage exclusion criteria (individuals whose BMI was ≤18 kg/m^2^, or who had a mean blood pressure ≥160/100 mmHg – those routinely excluded by the Imperative Health system as a safety precaution). This was explained to potential participants prior to their attendance at the measurement visit in the information sheet and also during the telephone call. Individuals who met all inclusion criteria continued with the visit. All baseline information was collected prior to randomisation. Participants had anthropometric and biological measurements taken (see Measures section and Table 1 for further details). Participants then completed a treadmill exercise test which was terminated when 80% of their age-predicted maximum heart rate (i.e. 208 minus 0.7*age) was reached. Predicted maximal cardio-respiratory fitness (VO_2max.pred_) was estimated using extrapolation of the heart-rate to VO_2_ relationship to age-predicted maximal heart rate. Participants were asked to provide demographic information and to complete a number of questionnaire measures (see Measures section and Table 1). Anthropometric and clinical measurement values were concealed from participants unless they specifically asked to see the results, thereby minimising the possibility of behaviour change associated with clinical feedback and to maximise participant retention at follow-up. Before leaving the measurement centre, participants were fitted with a combined movement and heart rate monitor (Actiheart, CamNtech, Cambridge, UK) and were instructed to wear the monitor for six days and nights continuously. They were instructed on how to change ECG electrodes (supplied), both verbally and in writing with depiction of correct placement. In the event that an insufficient amount of valid data was collected from the combined monitor following two separate wear periods, the participant was not able to continue in the study.

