#### Randomisation, allocation concealment and blinding

Once the combined monitor had been returned and the recorded data checked for quality and quantity (≥35 hours), participants were randomly allocated to one of the four study groups (Control, Diary, Activity Band or Activity Band Plus). Randomisation lists were prepared using Stata [25] within strata defined by age (<45, ≥45 years), sex and BMI (<27, ≥27 kg/m^2^) using a block size of 8. Participants in the ‘Control’ and ‘Diary’ groups were sent their randomisation allocation by internal post. Participants in the ‘Activity Band’ and ‘Activity Band Plus’ groups were told their allocation at their place of work and were given the necessary equipment and instructions on how to proceed during the 12 week intervention. The measurement team were blinded to the participants’ group allocation throughout the trial.

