##### Anthropometric measures

Height was measured without shoes using a wall-mounted fixed rigid stadiometer. Weight and body fat percentage were measured using a bio-electrical impedance monitor without shoes and in light indoor clothing (Tanita BC-418MA). Waist circumference was estimated as the mean of two measurements taken with a D-loop measuring tape placed halfway between the lowest point of the rib cage and the anterior superior iliac crest with the participant in a standing posture and in light indoor clothing. If the two measurements varied by more than 3 cm a third measurement was taken and the mean of the three measures used.

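### BMI is split at its median for the subgroup analysis of both co-primary outcomes, which costs about 36% of the information on a linear BMI trend if BMI is normal

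*Protocol article*

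**What the plan says.** The subgroup plan is a single sentence in the Statistical analysis section of the protocol article: "Subgroup analyses by sex and BMI (below/above median value) will be investigated for the 2 co-primary outcomes only". It fixes the form in which BMI enters, as two groups cut at the sample median. No other section adds an analysis of effect modification with BMI kept continuous.

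BMI is not collected in categories. Height is taken with a stadiometer, and the Anthropometric measures section adds: "Weight and body fat percentage were measured using a bio-electrical impedance monitor without shoes and in light indoor clothing". The Baseline assessment section places both measurements before randomisation and uses the resulting value for an exclusion: "individuals whose BMI was ≤18 kg/m^2^, or who had a mean blood pressure ≥160/100 mmHg". Randomisation also uses a BMI cut, but a fixed one: "sex and BMI (<27, ≥27 kg/m^2^) using a block size of 8". The median is therefore a second, data-dependent cut that the stratification does not call for.

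**The concern.** Splitting a continuous modifier treats everyone within a half as alike. A participant just above the median counts the same as the heaviest participant in the trial. If the effect of an intervention changes gradually with BMI, the contrast between halves is a less precise way of finding that change than a slope on the measured value.

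Sex and BMI are the only effect modifiers named, and they are examined only for the co-primary outcomes. BMI is a reasonable candidate, because the Activity Band Plus arm adds weighing scales, calorie monitoring and weight goals to the activity feedback. The trial is sized for main comparisons, so any interaction test starts with limited power. What is at stake is avoidable loss of precision on that one question. The co-primary tests and their intervals are unaffected.

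**Working it through.** **1. The plan's own figures.** The document states no power for the subgroup analysis, so the sample size is checked first. Inputs from the Sample size section: for PAEE, an SD of 0.076 kJ/kg/min and a baseline to follow-up correlation of 0.58, both taken from ProActive. The unadjusted claim reads: "100 participants per group completing follow-up would allow detection of a difference of 0.03 kJ/kg/min in PAEE". With ANCOVA adjustment the claim becomes: "100 participants per group at follow-up would enable detection of a difference between groups in mean PAEE of 0.025 kJ/kg/min". For fitness, the SD is 1.0 L/min, the correlation 0.88 and the difference 0.19 L/min. Power is 80% at a 5% level, taken as two-sided.

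- Detectable difference = (1.960 + 0.842) × SD × √(2/n), with n = 100 per group.
- PAEE, unadjusted: 2.802 × 0.076 × √(2/100) = 0.0301, against 0.03 stated.
- PAEE, ANCOVA: residual SD = 0.076 × √(1 − 0.58²) = 0.0619, giving 0.0245, against 0.025 stated.
- Fitness, ANCOVA: residual SD = 1.0 × √(1 − 0.88²) = 0.475, giving 0.188, against 0.19 stated.

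The stated figures reproduce. They concern main comparisons between groups.

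**2. Information kept by the split.** When the effect is linear in BMI, the share of interaction information kept is the squared correlation between BMI and its above-median indicator.

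- Normal BMI: correlation = φ(0)/0.5 = 0.399/0.5 = 0.798. Squared, this is 2/π = 0.637, a loss of 36.3%.
- Right-skewed BMI (lognormal, log-SD 0.12 to 0.22, values of 18 or below removed to match the exclusion; simulated): loss 37.0% to 38.8%.
- Uniform BMI: correlation = (1/8)/(√(1/12) × 1/2) = 0.866. Squared, this is 0.75, a loss of 25%.
- True step at the median: no loss, since the indicator is then the correct modifier.

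The article reports no BMI distribution, so all these shapes are assumed.

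**3. Effect on power, normal BMI.**

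- 1-df interaction: the noncentrality for 80% power is 2.802² = 7.85. After the split it is 7.85 × 0.637 = 5.00, and power is Φ(√5.00 − 1.96) = Φ(0.276) ≈ 61%.
- 3-df arm × BMI test: the noncentrality for 80% power is 10.90. After the split it is 10.90 × 0.637 = 6.94, and power is about 59%.
- A simulation with 100 per arm in two arms gave 79% power with continuous BMI and 59% after the split, for the same true slope. With no interaction, both tests rejected in about 5% of runs.

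**4. A case scaled to the plan's own difference.** Suppose the effect differs between the two BMI halves by the whole main-effect detectable difference, with 50 per arm in each half.

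- Split: the standard error is SD × √(4/50) and the true difference is 2.802 × SD × √(2/100). Their ratio is 1.401, the noncentrality is 1.96, and power is about 29%.
- Continuous: the noncentrality is 1.96/0.637 = 3.08, and power is about 42%.

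**The case against.** The strongest reply is that this is largely a matter of preference in a subsidiary analysis. The article sizes the trial for main comparisons and never claims 80% power for an interaction. In the scaled case above, power is low either way, at 29% or 42%, so the change does not make the BMI question conclusive. A median split gives two equal groups that are easy to report. A linear term assumes a shape and can be pulled by a few participants with extreme BMI. The loss is also conditional, at 25% for a flat distribution and nil for a true step.

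Much of this stands, and it limits the weight of the point. It does not remove it. The article gives no reason to expect a step at a value set by whoever enrols. Linearity can be checked, and the two-group estimates can still be shown.

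A reader might go further and infer that each half will be tested on its own, so that the trial will often report an effect in one BMI group only. The document does not support this. It says that subgroup analyses will be investigated, and it neither states nor rules out an interaction test. That detail is commonly left to a full protocol or analysis plan, which is not shown. If the halves are compared by an interaction test, the split costs power and leaves the false-positive rate at about 5%. For the same reason, no number of subgroup intervals can be attributed to the plan, because the sentence specifies no pairwise contrasts. Sex is binary, so nothing is lost there.

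**Conclusion.** The point holds as a modest one about efficiency. The plan explicitly fixes a median split of a modifier that is measured continuously before randomisation. For a roughly linear change of effect with normal BMI, the split loses about 36% of the interaction information and takes a 1-df interaction from 80% to about 61% power. Across the other shapes considered, the loss runs from 39% (strongest right skew) through 25% (uniform) to none (true step at the median). The result rests on approximate linearity and on an assumed BMI distribution. It is a cheap improvement to a subsidiary analysis, with no bearing on the validity of the co-primary tests.

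**What to change.** In the Statistical analysis section, state that effect modification by BMI will be assessed by adding continuous, centred BMI and arm × BMI terms to the ANCOVA for each co-primary outcome. Inference would come from the 3-df arm × BMI test, with pairwise slope differences and 95% confidence intervals. Keep the below/above-median estimates for display only.

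The cost is one sentence and one extra set of model terms per co-primary outcome, using data already collected. The downside is the linearity assumption and some sensitivity to extreme BMI values, which a quadratic term can check.

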#### Interventions

##### Control group

Participants randomised to this group received no intervention.

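### The secondary Per-Protocol analysis selects participants on use in the three intervention arms and on nothing in Control, so its contrasts with Control are not randomised comparisons

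*Protocol article*

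**What the plan says.** All of this is in the Statistical analysis section of the protocol article unless another section is named.

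- Primary population: "The primary analysis of outcomes will use an Intention-To-Treat population, which includes all participants in the group to which they were randomised".
- Secondary population: "A secondary analysis of outcomes will use a Per-Protocol (PP) population".
- Diary arm criterion: "degree of completion of the paper-based physical activity diary (for the Diary group").
- Criteria for both band arms: "total number of days in which physical activity was recorded on the accelerometer band from Imperative Health (Activity Band and Activity Band Plus groups") and "the total number of times the Imperative Health website was visited (Activity Band and Activity Band Plus groups").
- Control arm: no criterion is listed. The Control group section explains why there is nothing to adhere to: "Participants randomised to this group received no intervention".
- Timing of the cut-offs: "Degree of usage/completion will be defined once clean data are available (but before the start of any trial analyses), when the distributions can be inspected".
- Contrasts: the model yields estimates and "95% confidence intervals for each of the 6 pairwise comparisons", three of which are against Control.

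The section gives no adjustment for the selection and no caution about how the Per-Protocol contrasts should be read.

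**The concern.** Every listed criterion is a behaviour that occurs after randomisation and is observed only in an intervention arm. Participants who keep up the diary, wear the band or visit the website are likely to differ from those who do not in motivation, health and circumstances. Those who stop are removed from the intervention arms, while their counterparts in Control, who cannot be identified, remain. Adjusting for the baseline outcome does not remove this, because people with the same baseline can differ in how they would have changed anyway.

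The cut-offs can be settled in a later document, but no cut-off restores comparability with Control, since the imbalance lies in which arms are filtered at all.

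Contrasts between intervention arms are affected too. Diary and band participants are filtered by different measures. The two band arms share one rule, but Activity Band Plus users have more reasons to visit the website (meal plans, food diary, activity planner, coaching), so the people that rule keeps may differ between the arms. The direction of any resulting bias cannot be determined.

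At stake is a secondary result that could show an apparent benefit, or an apparent ranking of the interventions, that selection alone has produced.

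**Working it through.** **Inputs from the Sample size section.** PAEE: SD 0.076 kJ/kg/min, baseline to follow-up correlation 0.58, detectable difference 0.025 with 100 per group. Fitness: SD 1.0 L/min, correlation 0.88, detectable difference 0.19 with 100 per group. Power is 80% at the 5% level, taken as two-sided.

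**Reproducing the plan's figures.** Residual SD = SD × √(1 − r²).

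- PAEE: 0.076 × √(1 − 0.58²) = 0.0619 kJ/kg/min. Detectable difference = (1.96 + 0.84) × 0.0619 × √(2/100) = 0.0245, stated as 0.025.
- Fitness: 1.0 × √(1 − 0.88²) = 0.475 L/min. Detectable difference = (1.96 + 0.84) × 0.475 × √(2/100) = 0.188, stated as 0.19.

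Both agree, so these residual SDs are a fair scale for the bias.

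**Assumptions not in the documents.** The true effect is zero. A share p of an intervention arm is retained, being those with the highest use; p runs from 0.4 to 0.8. Use and the baseline-adjusted outcome are jointly normal with correlation ρ from 0.1 to 0.3. All controls are kept. The same ρ range is applied to both outcomes.

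**Formula.** Bias in residual SD units = ρ × φ(c) / p, where c is the (1 − p) quantile of the standard normal and φ its density.

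| p | ρ | φ(c)/p | Bias, residual SD | PAEE, kJ/kg/min (share of 0.025) | Fitness, L/min (share of 0.19) |
|---|---|---|---|---|---|
| 0.8 | 0.1 | 0.350 | 0.035 | 0.0022 (9%) | 0.017 (9%) |
| 0.6 | 0.3 | 0.644 | 0.193 | 0.0120 (48%) | 0.092 (48%) |
| 0.4 | 0.3 | 0.966 | 0.290 | 0.0179 (72%) | 0.138 (72%) |

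With ρ = 0 the bias is zero; with negative ρ the sign reverses.

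**Check by simulation.** The ANCOVA on change in PAEE was simulated with no true effect, 100 controls against 100p retained users, and 4,000 runs per scenario.

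| p | ρ | Mean spurious difference, kJ/kg/min | False-positive rate (nominal 5%) |
|---|---|---|---|
| 0.6 | 0 | 0.0001 | 5% |
| 0.6 | 0.2 | 0.0075 | 11% |
| 0.6 | 0.3 | 0.0121 | 22% |
| 0.5 | 0.3 | 0.0146 | 27% |

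The simulated biases match the formula closely (0.0080, 0.0120 and 0.0148 for the last three rows).

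**The case against.** The strongest reply is that a secondary Per-Protocol analysis is conventional, Intention-to-Treat is explicitly primary, and no stated decision rests on the Per-Protocol result. That stands, and it limits the importance of the point. A condensed article may also leave cut-offs and interpretive wording to an analysis plan not shown here. That stands for the cut-offs, but the selection variables and the arms they apply to are already fixed in the article.

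A reader might infer more than the documents support in four respects:

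- *That the band criterion selects on the outcome itself.* The same measure is listed under Degree of intervention use, and Table 1 describes it as use of the band. It may simply count days with band data, that is, wear. The outcomes come from other instruments: the combined heart-rate and movement monitor and the treadmill test.
- *That the analysis is certainly biased towards benefit.* This needs a positive correlation between use and outcome, and the documents give none.
- *That each intervention arm has its own rule.* The two band arms share the same criteria; only Diary differs.
- *That the cut-offs are chosen to suit the results.* They are to be set from usage distributions before any trial analysis begins, which guards against outcome-driven choices.

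The remedy has limits as well. A complier-average effect assumes that allocation does nothing for people below the use threshold, which is doubtful for partial users. Controls on a shared campus could self-monitor or use activity websites. The estimator also leaves the three contrasts between intervention arms unaddressed.

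**Conclusion.** The point holds for the secondary analysis. As written, the three Per-Protocol contrasts with Control compare participants selected on use with an unselected arm, and the plan neither adjusts for this nor warns of it. The direction of bias is an inference: towards benefit if use and the baseline-adjusted outcome are positively correlated, none if they are unrelated.

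The range of 9–72% of the detectable differences rests on the assumed retained share and correlation. Its upper end is the extreme corner (40% retained, correlation 0.3), not a typical value. The same correlation range was applied to fitness for want of anything better.

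For contrasts between intervention arms, selection can distort the comparison, but neither size nor direction can be derived. The primary analysis and its conclusions are untouched. The change is worth making because better-protected estimates against Control can be had from data already collected.

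**What to change.** 1. Make the secondary adherence analysis a complier-average causal effect for each intervention versus Control, with randomised allocation as the instrument, use of the allocated intervention as the exposure, and the same baseline covariates as the primary model.
2. Define use by band wear days or uploads, log-ons, and diary completion. State explicitly that a recorded day means a day with band data, if that is what is meant. Keep the existing commitment to fix thresholds before outcome analysis.
3. State the exclusion restriction and repeat the analysis over a range of use thresholds, because the restriction is doubtful for partial users.
4. Check for contamination in Control with items already collected at follow-up: self-monitoring behaviour, use of activity advice websites, and contact with other participants.
5. If Per-Protocol results are still shown, including the three contrasts between intervention arms, label them observational and supportive only.

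The cost is a change of wording and a standard two-stage estimator, with no new data. The price is precision. If non-use is one-sided and the sampling error in the proportion of users is ignored, intervals are about 1/p times as wide as those from Intention-to-Treat: 1/0.8 = 1.25 times with 80% users and 1/0.4 = 2.5 times with 40%. The exclusion restriction cannot be tested and has to be stated.
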